### Intervention and control arms

#### Intervention

*Finding My Way* is a 6-week password-protected CBT internet application comprised of three main components: (1) psycho-education, (2) cognitive-behavioural worksheets/strategies including worksheets, quizzes, relaxation and meditation exercises, and (3) survivor testimonials. Each week a new module is released to participants, and participants can continue referring back to previous modules throughout the study.

The 6 modules address: (i) starting treatment – working with your medical team, covering assertive communication and decision making, (ii) coping with physical symptoms and side effects – including fatigue, pain, insomnia, and provides activity pacing worksheets, and relaxation audiotracks; (iii) coping with emotional distress – which covers depression, anxiety, anger and stress, and provides cognitive restructuring diaries, and mindfulness audio-tracks; (iv) body image, identity and sexuality – with psychosexual worksheets, and therapeutic writing activities; (v) your family and friends – comprising further assertive communication and needs assessment worksheets; and (vi) completing treatment, which includes self-management strategies to facilitate healthy lifestyles.

A private online note-taking feature, mood monitoring/management, and a resource section with links to reputable cancer-related organisations and other health websites are also available throughout the duration of the program. The program is outlined in Table 1.

**Table 1 Tab1:** ***Finding My Way***
**content**

*Module*	*Topics covered*	*Worksheet/Activities*
Starting treatment	Working with your medical team, treatment planning	Assertive communication, Decision making
Physical symptoms	Coping with side effects including fatigue, pain, insomnia	Activity pacing, Relaxation exercises
Emotional distress	The emotional rollercoaster, including depression anxiety, anger and stress	Cognitive restructuring, Mindfulness exercises, Therapeutic writing
Identity	Concerns regarding body image, loss or changes in perceived identity, intimacy and sexuality	Psychosexual worksheets, Therapeutic writing
Family & Friends	The range of support concerns that arise, including identifying support people, impact on children and partners	Assertive communication, Needs assessment
Completing treatment	Commencing preventative health behaviours, follow-up care planning	Self-management, Goal setting
Booster	Summary of key themes from previous 6 topics. Links back to key webpages.	Links back to key worksheets (goal setting, cognitive restructuring, relaxation, communication).

#### Attention control

An information-only version of *Finding My Way,* developed to provide an appropriate attention control for the study, covers the same 6 module topics without any of the worksheets, activities, relaxation exercises, or note-taking feature. Our previous research indicates that an attention control condition does not significantly reduce distress [29], and provides a more rigorous test of the intervention.

### Outcomes

Primary, secondary and moderator outcomes are assessed using online self-report questionnaires. Baseline questionnaires are completed upon enrolment/ prior to randomisation. Post treatment questionnaires are completed at the conclusion of the sixth module (seven weeks after completing the baseline survey), and follow-up questionnaires are completed approximately 3 months and 6 months after treatment completion.

#### Primary outcome: distress

The primary outcome for this study is distress, measured as general distress and as cancer-specific distress. General distress is measured using the total scale score of the 21-item Depression Anxiety Stress Scale – short form (DASS: [33]), which assesses levels of anxiety, depression and stress over the previous week on a four-point scale ranging from (0) Did not apply to me at all to (3) Applied to me very much, or most of the time. Cancer-specific distress is measured using the 17-item Posttraumatic Stress Scale-Self Report [34], which measures on a 4-point scale (*0 = Not at all or only one time, 3 = 5 or more times per week / almost always*), the severity of each DSM-IV post-traumatic stress disorder symptom criterion in terms of how often respondents experienced each symptom in the previous week. For this study, the measure was adapted in order to reflect cancer diagnosis as the stressor.

#### Secondary outcomes

Secondary outcomes for this study include Health-Related Quality of Life (HRQOL), coping, and the economic impact of the intervention in terms of Health Service Utilisation. HRQOL is measured using the European Organisation for Research and Treatment of Cancer Quality of Life Core Questionnaire [35], a 30-item comprehensive health related quality of life assessment for cancer patients which yields a global QOL score, and five functional subscales (physical, emotional, social, role, cognitive).

Coping is measured with the mini-Mental Adjustment to Cancer Scale (mini-MAC: [36]), a 29-item scale yielding 5 factors: Fighting Spirit, Helplessness/Hopelessness, Anxious Preoccupation, Fatalism, and Cognitive Avoidance. Items are responded to on a 4-point scale ranging from ‘*definitely does not apply’* to ‘*definitely does apply*’.

Health Service Utilisation is examined using the 17-item Health Service Utilisation Questionnaire [37], which assesses health service use in the previous 12 months in terms of whether patients have been hospitalised and the number of visits to doctors and other health professionals. Hospitalisation is indicated as *no*/*yes day only*/*yes spent at least one night* (with number of days then recorded). Visits to GPs/hospital doctors/specialist doctors are indicated on a 7-point scale ranging from *none* to *25 or more times*, and utilisation of other health professionals (e.g. physiotherapist) is indicated as *yes* or *no*.

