
## Discussion

Internet-based self-help modalities represent one means of overcoming existing barriers to cancer patients accessing supportive care and psychosocial services, including the lack of such services within the public health system, particularly for rural patients, and barriers to attendance even where such services are provided. However, previous studies examining the efficacy of web-based self-help modalities for cancer populations have suffered from a range of limitations including (1) lack of an established psychological model (such as CBT) as the basis for the program, (2) lack of a control condition (3) small sample size and consequent lack of power for analyses, (4) lack of follow-up analysis over time, (5) examining efficacy of programs for one cancer type (i.e. breast cancer) only, as opposed to heterogeneous cancer types, and/or (6) examining programs implemented after completion of cancer treatment, as opposed to soon after diagnosis when distress tends to be highest and psychological treatment most warranted.

To our knowledge, *Finding My Way* is unique in offering an iCBT intervention applicable to individuals with heterogeneous cancer types soon after diagnosis. The large scale of this national multi-site RCT will therefore enable examination of the efficacy of such a program in reducing patient distress, improving coping and health related quality of life, and reducing health service utilisation in individuals with a range of cancer diagnoses. Furthermore, this study offers the important contribution of evaluating potential moderators of change. This information can be of benefit clinically when determining who to refer for online-interventions (versus who may be more suitably treated via other modalities) as well as benefitting future research via the refinement of inclusion and exclusion criteria, improving trial stratification and increasing power [30]. Indeed, it has been suggested that results of treatment trials are often weak because moderators of treatment are not examined, thus they should be part and parcel of any treatment study [30]; however, few studies have specifically examined moderators of psycho-oncology interventions.

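### Health service use is recalled over 12 months at follow-ups 7 weeks to about 7.6 months after baseline, so each answer includes pre-randomisation use and any effect is attenuated

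*Protocol article*

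**What the plan says.** Under Secondary outcomes, the article lists "the economic impact of the intervention in terms of Health Service Utilisation" beside quality of life and coping. The questionnaire "assesses health service use in the previous 12 months in terms of whether patients have been hospitalised", and also covers visits to doctors and other health professionals. Hospitalisation has three categories, with days recorded for overnight stays. Doctor visits are given on a seven-point scale whose top category is open at 25 or more. For the remaining professionals, "utilisation of other health professionals (e.g. physiotherapist) is indicated as" yes or no.

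On timing, the Outcomes section says that "Baseline questionnaires are completed upon enrolment/ prior to randomisation". The post-treatment questionnaire comes "seven weeks after completing the baseline survey", and "follow-up questionnaires are completed approximately 3 months and 6 months after treatment completion".

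Statistical analysis applies one linear mixed model, group by three post-baseline times with the baseline value as covariate, to every outcome variable. The Discussion expects the trial to examine efficacy in "improving coping and health related quality of life, and reducing health service utilisation in individuals with a range of cancer diagnoses".

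No shorter recall period is given for the follow-ups. The only adaptation of an instrument that the article describes is to the post-traumatic stress measure.

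**The concern.** The recall window is longer than the whole follow-up. No assessment falls 12 months or more after baseline, so every follow-up answer mixes use before randomisation, which the programme cannot have changed, with use after it. Once both sit in one answer, no later analysis can separate them.

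Entrants are on active treatment or, after surgery alone, within six months of diagnosis. The months before baseline may therefore hold admissions and frequent specialist contact. Someone who is already a yes on hospitalisation or on another professional, or already in a high visit band, because of that earlier use has little or no room to show a later difference. The linear model adds a smaller problem: a mean difference in category codes has no direct reading as visits or admissions.

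At stake is the trial's stated question about service use and its economic impact. A null result on this outcome could come partly from the recall window rather than from the programme.

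**Working it through.** The plan gives no sample size, power or expected effect for health service use, so there is no figure of its own to reproduce. Its 94 per group is for the distress outcome and is used below only as the number per arm.

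**1. Share of the window before randomisation.** Inputs: recall 12 months (Secondary outcomes); follow-ups at 7 weeks, 7 weeks + 3 months and 7 weeks + 6 months after baseline (Outcomes). Seven weeks is 49/30.44 = 1.61 months. With T the months since baseline, the share after baseline is f = T/12 and the share before is 1 − f.

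| Assessment | T (months) | f | 1 − f |
|---|---|---|---|
| Post-treatment | 1.61 | 13.4% | 86.6% |
| 3 months | 4.61 | 38.4% | 61.6% |
| 6 months | 7.61 | 63.4% | 36.6% |

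**2. Relative effect seen, at a steady contact rate (assumption).** Observed reduction = true reduction × f. For a true 20%: 0.20 × 0.134 = 2.7%; 0.20 × 0.384 = 7.7%; 0.20 × 0.634 = 12.7%.

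**3. Range if the rate is not steady.** The article gives no contact rates. Let the pre-baseline rate be k times the later rate. The pre-randomisation share of contacts is s = (12 − T)k / [(12 − T)k + T], and a true 20% reduction appears as 0.20 × (1 − s).

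| Assessment | s, k = 0.5 to 2 | 20% appears as |
|---|---|---|
| Post-treatment | 76.3% to 92.8% | 4.7% to 1.4% |
| 3 months | 44.5% to 76.2% | 11.1% to 4.8% |
| 6 months | 22.4% to 53.6% | 15.5% to 9.3% |

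Over this range, only at post-treatment is it secure that most contacts precede randomisation.

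**4. Precision for count-like data, with the planned covariate.** Assume independent Poisson contacts at a constant rate and work in weeks (T = 7, 20, 33; window 52). The baseline and follow-up windows overlap by 52 − T = 45, 32 and 19 weeks. The residual variance after baseline adjustment is proportional to 52 − overlap²/52, against T for a window that starts at baseline. The ratio is the sample-size multiple:

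- Post-treatment: (52 − 45²/52)/7 = 13.06/7 = 1.9
- 3 months: (52 − 32²/52)/20 = 32.31/20 = 1.6
- 6 months: (52 − 19²/52)/33 = 45.06/33 = 1.4

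As an illustration with 94 per arm, take an assumed effect of 0.42 SD on use since baseline, which has 82% power when asked directly. Power falls to 56%, 62% and 69%.

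**5. Yes/no hospitalisation.** Assume later risks of 30% and 15% (direct power 70% with 94 per arm). Let a proportion p already answer yes because of pre-baseline use, independently of later use. The observed risk is 1 − (1 − p)(1 − later risk).

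| p | Observed risks | Difference | Power |
|---|---|---|---|
| 50% | 65.0% v 57.5% | 7.5 points | 18% |
| 70% | 79.0% v 74.5% | 4.5 points | 11% |
| 90% | 93.0% v 91.5% | 1.5 points | 6% |

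The values of p are assumptions. The 15-point true difference shrinks by the factor 1 − p.

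**The case against.** The strongest reply is that randomisation balances pre-baseline use, so including it does not bias the comparison. For true counts the absolute difference in contacts, which is what an economic reading needs, is unchanged; only the percentage shrinks. The overlap between baseline and follow-up windows is not purely a fault either, since it is what lets the baseline covariate remove pre-randomisation noise. All of this stands. It does not rescue the yes/no items, the hospitalisation category or the capped bands, because these do not add up over time as counts do.

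A reader might infer that the effect is diluted away, or that the required sample rises about 55, 6.8 and 2.5 times. The documents support neither. At 6 months about 63% of the window follows randomisation. The large multiples are (52/7)², (52/20)² and (52/33)². They hold only if the SD grows in proportion to window length, which means that each person's use is perfectly stable, and they ignore the covariate planned under Statistical analysis. Under that stability the covariate would remove almost all of the pre-randomisation variation. Independent Poisson contacts without the covariate give 52/7 = 7.4, 52/20 = 2.6 and 52/33 = 1.6; with it, 1.9, 1.6 and 1.4.

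It can also be said that use of this questionnaire at every follow-up is inferred. The Abstract and Outcomes speak of questionnaires in general, and some measures are baseline only. The inference is reasonable, because the group-by-time model covers each outcome variable and no baseline-only limit is placed on this one. Even if it were asked only at 6 months, 37% of the window would precede randomisation.

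Finally, health service use is secondary, is not named in the hypotheses and does not enter the sample size, and item-level models are commonly left to an analysis plan. This lowers the severity and makes the modelling remark subsidiary. It does not cover the recall period, which is a data-collection choice that the article states.

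**Conclusion.** The concern holds as attenuation of a secondary outcome. On the stated timings, about 87%, 62% and 37% of the 12-month window precedes randomisation at post-treatment, 3 months and 6 months; these shares need only the assumption that the questionnaire is repeated at follow-up. That a 20% reduction appears as 2.7%, 7.7% and 12.7% further assumes a steady contact rate, and the range above shows how far this moves. The loss is moderate for count-like data under the planned covariate and can be severe for the yes/no, hospitalisation and banded items.

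It would be wrong to conclude that the group comparison is biased, or that a null result would necessarily be an artefact. This is a should-fix point: it limits what the trial can say about service use and leaves the primary distress conclusion untouched.

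**What to change.** Keep the 12-month recall at baseline only. At each follow-up, ask about use since a calendar date displayed on screen: the date of the participant's last completed survey, or the baseline date if none has been completed since. Completed on schedule, this gives windows of about 7 weeks, 3 months and 3 months that start at baseline and do not overlap. The date anchor keeps the window defined when a survey is missed, which matters with 21% attrition expected. Record each window's length and allow for it in the analysis.

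Analyse the yes/no items with logistic models, and the visit bands and hospitalisation category with ordinal models, in place of the linear mixed model.

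For participants already surveyed with the 12-month wording, analyse their answers separately, treat the 6-month answer as the least diluted, and do not pool it with answers to the new wording.

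The cost is a changed question stem in an online form and a minor amendment. The downside is that the adapted window departs from the published form of the instrument. If the wording cannot be changed, the article should limit its statements on service use and economic impact accordingly.

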#### Moderators of outcomes

Participant and medical characteristics, availability of social support, information-seeking preferences, emotion regulation, vulnerability to cancer-distress, adherence to the program, and participant satisfaction are assessed as postulated moderators of program efficacy.

Participant and medical characteristics are assessed at baseline only, and consist of age, marital status, occupational status, annual gross income, level of educational attainment, area of residence (rural/urban, state), ethnicity, cancer type, time since diagnosis, treatment received (surgery, chemotherapy, radiotherapy, hormonal therapy, other), any other chronic health conditions, and other support-services accessed.

Availability of social support is assessed using the 20-item Medical Outcome Study Social Support Survey [38], which consists of four subscales: emotional/informational, tangible, affectionate, and positive social interactions, with availability of the support type listed in each item rated on a 5-point scale (*1 = none of the time, 5 = all of the time*).

Information seeking preferences in terms of the type and amount of cancer information sought by patients is measured by the Miller Behavioral Style Scale scale [39]. This scale identifies information seekers who look for and amplify threat-related cues (monitors) and distracters who avoid and minimize such cues (blunters), and has been used extensively in cancer populations. The scale asks the respondent to imagine two stress-evoking scenarios, each of which is followed by eight statements that describe different ways of coping with the stressor, with four statements being of a monitoring or information-seeking variety and four of a blunting or information-avoiding variety. Respondents are asked to check all statements that apply to them.

Vulnerability to distress is assessed using the Difficulties in Emotion Regulation Scale [40], a 36-item measure of difficulties in emotion regulation across six dimensions, namely a) lack of awareness of emotional responses, b) lack of clarity of emotional responses, c) non-acceptance of emotional responses, d) limited access to emotion regulation strategies perceived as effective, e) difficulties controlling impulses when experiencing negative emotions, and f) difficulties engaging in goal-directed behaviours when experiencing negative emotions. Participants respond to each item on a 5-point scale (*1 = almost never, 5 = almost always*).

Adherence to the study is measured in two ways. First, the self-help compliance scale [41] measures participant self-reported engagement with program’s (i) information, (ii) worksheets, and (iii) weekly time usage. Second, website use indicators are tracked on the website itself, including: number of visits, length of time logged in, and number of modules and worksheets completed.

Finally, levels of satisfaction with the website will be assessed as a measure of whether this intervention improved psychosocial support for patients. Qualitative feedback will be gathered within the website, and at follow-up assessments.

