**Methods/Design:**

The study is a multi-site Randomised Controlled Trial (RCT) seeking to enrol 188 participants who will be randomised to either the *Finding My Way* Intervention or an attention-control condition. Both conditions are delivered online; with 6 modules released once per week, and an additional booster module released one month after program-completion. Participants complete online questionnaires on 4 occasions: at baseline (immediately prior to accessing the modules); post-treatment (immediately after program-completion); then three and six months later. Primary outcomes are general distress and cancer-specific distress, with secondary outcomes including Health-Related Quality of Life (HRQoL), coping, health service utilisation, intervention adherence, and user satisfaction. A range of baseline measures will be assessed as potential moderators of outcomes. Eligible participants are individuals recently diagnosed with any type of cancer, being treated with curative intent, aged over 18 years with sufficient English language literacy, internet access and an active email account and phone number. Participants are blinded to treatment group allocation. Randomisation is computer generated and stratified by gender.

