#### Statistical analysis

Quantitative data will be analysed using the Statistical Package for the Social Sciences (SPSS) Version 17.0. Baseline differences between groups will be investigated using t-tests for continuous measures and *χ*^2^ tests of independence for categorical measures. Linear Mixed Effects Models (LMEM) will be employed to examine the efficacy of the intervention. The LMEM calculates a regression line for each individual while controlling for baseline observation (fixed main effects). Baseline observations will be entered as covariates to eliminate the influence of baseline variability, resulting in a 2 (group: intervention; control) X 3 (time: post-program; 3-month follow-up; 6 month follow-up) fixed effects model for each outcome variable, with random effects accounting for individual variation. This approach effectively equalises conditions at baseline and consequently allows for direct comparison between conditions at each follow-up point. In this context, (a) interactions between condition and time, (b) main effects of group and (c) post-hoc pairwise comparisons at each follow-up point are all indicators of intervention effects. This analysis offers the benefit of estimation maximisation; it provides joint modelling for each participant of observed and missing data based on maximising likelihood for population parameters as a function of the observed data. LMEM analyses are therefore robust with respect to handling missing data and unbalanced designs in longitudinal research as all participants with at least one observed *post-treatment* data point are included. That is, as baseline data is entered as a covariate, participants who do not complete any of the post-program assessments are not retained. To overcome this limitation and ensure this trial adopts a fully intention-to-treat design, multiple imputation will be performed for participants with only baseline-data. Therefore all participants, regardless of missing data at one or more assessment points, will be included in analyses and accurate parameter estimates obtained. Within-group effect sizes and reliable change indices will be calculated to provide a measure of the magnitude and clinical significance of changes respectively. To test for moderation, separate LMEM analyses will be conducted for each combination of moderator and outcome variable, where the moderator and group are entered in model 1 to control for main effects. The product term is then entered in model 2, to represent the interaction between group and moderating variable, and will indicate the moderating effect.

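### Adherence and satisfaction arise after randomisation but are listed as moderators; their group-by-moderator interactions can be biased, and the list conflicts with the abstract and the hypotheses

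*Protocol article*

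**What the plan says.** All references are to the protocol article.

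- **Moderators of outcomes** names participant and medical characteristics, social support, information-seeking preferences, emotion regulation and vulnerability to distress. It then adds that "adherence to the program, and participant satisfaction are assessed as postulated moderators of program efficacy".
- The same section measures adherence in two ways: self-reported engagement with the program's "i) information, (ii) worksheets, and (iii) weekly time usage", and tracked website use, namely "number of visits, length of time logged in, and number of modules and worksheets completed". On satisfaction it says that "levels of satisfaction with the website will be assessed as a measure of whether this intervention improved psychosocial support for patients".
- **Enrolment** places randomisation after the baseline questionnaire and before any module is opened.
- **Attention control** says that the control site "covers the same 6 module topics without any of the worksheets, activities, relaxation exercises, or note-taking feature".
- **Statistical analysis** says that "separate LMEM analyses will be conducted for each combination of moderator and outcome variable". Moderator and group enter first and their product second. No exception is made for variables measured after randomisation.
- **Abstract, Methods/Design** says: "A range of baseline measures will be assessed as potential moderators of outcomes". It counts adherence and user satisfaction among the secondary outcomes.
- **Aims and hypotheses** names three moderators: social support, cognitive vulnerability to distress and motivation to seek information.

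**The concern.** A product term describes who benefits more from an intervention only if the moderator could not have been changed by allocation. Adherence and satisfaction do not exist until a participant has used the assigned site, and the two sites differ by design. High users of an activity-based site and high users of an information-only site may be different kinds of patient. Comparing the arms at a given level of use is then no longer a comparison of randomised groups.

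Moderation is the trial's stated secondary aim, and the Discussion intends the results to help decide whom to refer. A selection effect could be read as evidence that the program works for those who use it. Usage and satisfaction are in any case unknown at referral, so even an unbiased interaction with them would not serve that purpose.

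**Working it through.** The plan gives no figure for this analysis, so there is none to reproduce. The planned 188 participants (94 per group) serve only as the size of the illustration in step 3.

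**1. Timing and role of the two variables**

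| Source | Adherence and satisfaction | Moderators |
|---|---|---|
| Abstract, Methods/Design | secondary outcomes | baseline measures |
| Aims and hypotheses | not named | three factors, neither of these |
| Moderators of outcomes | moderators | a longer list that includes both |
| Enrolment | can arise only after randomisation | not addressed |
| Statistical analysis | not treated separately | every one gets a product term |

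The first three rows cannot all stand.

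**2. Worksheets completed as the moderator**

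Let G = 1 for intervention and 0 for control, and let W be the number of worksheets completed. The control site has none, so W = 0 whenever G = 0.

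- Control: G × W = 0 × 0 = 0 = W.
- Intervention: G × W = 1 × W = W.

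The product column is therefore identical to the main-effect column. Model 1 (intercept, baseline, group, W) has 4 columns and rank 4. Model 2 adds G × W and has 5 columns but still rank 4; a numerical check with 94 per group confirmed this. The interaction has no estimate. In model 1, the group coefficient becomes a contrast of intervention participants at zero worksheets with all controls.

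**3. Adherence measures that accrue in both arms (visits, time, modules)**

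Here the product term can be estimated, so the question is what it estimates when there is no moderation. None of the following inputs except the sample size and the 0.35 SD effect is in the documents; they are assumptions for illustration.

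- One follow-up, 188 participants with complete data, linear model adjusted for baseline, outcome in SD units.
- The same treatment effect of −0.35 SD for everyone.
- A latent prognosis, independent of the baseline score, with coefficient γ on the outcome (−0.3 or −0.5).
- An adherence score with SD 1 within each arm, correlated with prognosis a₀ in control and a₁ in intervention.

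Within an arm, the slope of outcome on adherence is γ × a. The product term therefore estimates γ × (a₁ − a₀), although the true moderation is zero. For example, −0.5 × (0.5 − 0) = −0.25. Simulation (4000 runs per setting, two-sided 5% test) gave:

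| a₀ | a₁ | γ | γ(a₁ − a₀) | simulated mean | false positives |
|---|---|---|---|---|---|
| 0.3 | 0.3 | −0.3 | 0 | −0.002 | 5.1% |
| 0.3 | 0.3 | −0.5 | 0 | 0.002 | 5.4% |
| 0 | 0.3 | −0.3 | −0.09 | −0.089 | 10.4% |
| 0 | 0.3 | −0.5 | −0.15 | −0.149 | 21.4% |
| 0 | 0.5 | −0.3 | −0.15 | −0.151 | 22.3% |
| 0 | 0.5 | −0.5 | −0.25 | −0.256 | 52.1% |
| 0.2 | 0.6 | −0.3 | −0.12 | −0.117 | 14.4% |
| 0.2 | 0.6 | −0.5 | −0.20 | −0.203 | 38.0% |
| −0.3 | 0.3 | −0.3 | −0.18 | −0.179 | 29.3% |
| −0.3 | 0.3 | −0.5 | −0.30 | −0.301 | 66.7% |

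The spurious interaction depends on the difference between arms in the adherence–prognosis relation. It disappears when that relation is the same in both.

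**The case against.** The strongest defence is that this is one misplaced entry in a list. The abstract assigns adherence and satisfaction to the secondary outcomes, no hypothesis mentions them, and moderation is itself secondary. That limits the consequence and shows how easily the text can be reconciled. It does not remove the problem, because Statistical analysis applies its product-term recipe to every moderator without exception.

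Several stronger readings are tempting, and the documents do not support them.

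- **That the interactions are certainly biased.** They can be; step 3 shows no bias when the relation is equal in both arms. Equality is hard to assume for two different websites, but the documents neither establish nor exclude it.
- **That adherence as a whole cannot be analysed.** The exact aliasing applies only if worksheet count is entered as its own moderator. The article does not say how adherence is scored. Visits, time and modules can all be estimated. The worksheet item of the compliance scale is self-reported, so control answers are not fixed at zero by design. Software would probably flag the redundant term rather than mislead silently.
- **That social support and emotion regulation might enter as post-baseline values.** The remark that characteristics are assessed at baseline only concerns when those are collected, and the abstract says that moderators are baseline measures.
- **That the moderation analyses are underpowered or produce too many false positives through multiple testing.** A low power figure would need a 50/50 binary moderator, which the article does not state; the three named moderators are measured by questionnaire scales. Multiplicity is a separate question and may be handled in an analysis plan that is not shown.

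**Conclusion.** The point holds as a defect of the secondary moderation analyses. As written, the plan treats two post-randomisation variables as moderators, in conflict with its own abstract and hypotheses. The resulting interactions are open to selection bias whose size cannot be derived from the documents. The 10% to 67% false-positive range rests entirely on assumed correlations that differ between arms, and shows only that the effect need not be small. The worksheet result is exact, but conditional on worksheet count being the moderator. A reader might infer that the trial's main result is at risk. It is not: the primary group comparison and the sample size of 188 do not use these variables.

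**What to change.** 1. In Moderators of outcomes, remove adherence and satisfaction from the moderator list.
2. Report both by arm as secondary or process outcomes, as the abstract already does. Add them to the main-text Secondary outcomes section, which does not name them at present.
3. In Statistical analysis, state that moderators enter as baseline values.
4. Present any relation between usage and outcome descriptively within the intervention arm, labelled non-causal. A complier-average analysis is not an easy substitute. Controls also work through six modules and the arms differ in several components at once, so its exclusion restriction would be doubtful.

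The cost is a few sentences of wording and one descriptive analysis. The trial gives up any claim that adherence moderates efficacy. The change should be made before outcome data are analysed by arm.
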